#### Secondary Objective

▪   To determine the prevalence and course of hypoperfusion and its effect on recurrent vascular events in patients with TIA 3 months after onset.

### Study Population and Setting

All patients will be recruited from the outpatient of the Neurology Department of Shanghai Fourth People's Hospital and Tongji Hospital; both are affiliated to Tongji University School of Medicine. TIA will be diagnosed by two experienced attending physicians in the Neurology Department.

### Inclusion Criteria

Aged 18 years or olderNo intracerebral hemorrhagePatients or their relatives are willing to participate in the study and provide written informed consentMeet the diagnostic criteria for transient ischemic attackPresent within 7 days of onset.

### Exclusion Criteria

The recent episode lasted more than 1 h but <4.5 h upon arrival at the hospitalPre-stroke mRS ≥ 2History of severe bleeding or major surgery within 30 daysConcomitant terminal illness with a life expectancy ≤12 monthsAny known hereditary or acquired hemorrhagic diathesis, coagulation factor deficiency, or intake of oral anticoagulants with INR > 1.7Platelet count <100,000/mm^3^Hemoglobin <10 g/dlSerum glucose level ≤50 mg/dlSevere renal insufficiency with creatinine clearance rate <30 ml/minPatients or their relatives refuse to or not available for MRI perfusion testUncooperative patients in 3-month follow-up.

### Recruitment and Consent

Patients suspected of clinical TIA will be recruited by attending general practitioners or neurologists at the time they present to the neurology clinic. They and/or their relatives will be asked whether they agree to be contacted by researchers regarding the possibility of participating in this study. If the patients and/or their relatives agree to do so, their eligibility will be assessed, and the detailed procedures of this study will be explained to them. Lastly, written informed consent will be obtained from them if they are eligible for this study.

### Procedures

Ninety patients will be recruited in the next 1.5 years based on the calculation of the authors. Baseline assessments will be completed when the participants visit the neurology clinic of Shanghai Fourth People's Hospital or Tongji Hospital. The first PWI will be completed within 24 h after onset, and the subsequent PWI will be completed on the 7th day ± 2. Three visits to the hospital are required, which include the first visit for randomization (baseline) and the next two for repeat PWI on day 7 ± 2 and follow-up on 90 ± 7 days. The incidence of recurrent vascular events will be collected from all the patients on the second and third visits. Meanwhile, etiological subtypes (large artery occlusive disease, small vessel disease, cardioembolism, etc.) should also be considered for reasons of early recurrent stroke (Purroy et al., 2007). Baseline and follow-up assessments are summarized in Table 1.

**Table 1 T1:** Trial schedule.

**Assessment**	**Screening (within 24 h of symptoms onset)**	**Visit 1**	**Visit 2**	**Visit 3**
		**Baseline**	**Day 7 ± 2**	**Day 90 ± 7**
Demographic characteristics	×			
ABCD2 score (for TIA)	×			
Modified Rankin Scale	×		×	×
Focused medical history	×^a^			
Current medications	×^b^		×	×
MRI scan	×			
MRI PWI		×	×	×
Laboratory tests	×			
Electrocardiograph (ECG)	×			
Inclusion/Exclusion criteria	×			
Signed informed consent	×			
AEs/SAEs^c^		×	×	×
Incidence of recurrence			×	×

*AE, adverse event; SAE, serious adverse event; TIA, transient ischemic attack; ABCD2, a risk assessment tool designed to improve the prediction of short-term stroke risk after transient ischemic attacks*.

a *Relevant existing data from admission to hospital will be reviewed and recorded into the CRF. Included are concomitant diseases and medical history*.

b *The medications used during the trial should be recorded*.

c *SAEs will be recorded from the time of informed consent. AEs of interest and endpoints will be collected from the time of admission to the hospital*.

### MRI Protocol

MRI is performed using a 1.5- or 3.0-T Avanto scanner (Siemens, Erlangen, Germany). The imaging protocol consists of DWI, PWI, FLAIR, and MRA. Imaging parameters are listed below. Axial EPI-DWI: TR = 3,600 ms, TE = 102 ms; FOV = 2.3 cm^2^, *b* value = 0 and 1,000 s/mm^2^; EPI factor = 192; matrix size = 192 × 192; bandwidth = 964 Hz/pixel; 19 slices, slice thickness = 5.5 mm. Axial FLAIR: TR = 4,000 ms, TE = 92 ms; FOV = 2.3 cm^2^; TI = 1532.6 ms; matrix size = 256 × 190; bandwidth = 190 Hz/Px; 18 slices, slice thickness = 5.5 mm. Axial EPI-PWI: TR = 1,590, TE = 32 ms; measurements = 50; FOV = 2.3 cm^2^; matrix size = 128 × 128; band width = 1,346 Hz/pixel; 19 slices, slice thickness = 5.5 mm. Gd-DTPA contrast agent (gadopentetate dimeglumine; Shanghai Pharmaceutical Corporation, Shanghai, China) is intravenously injected (0.2 mmol/kg body weight) at a rate of 4 ml/s after flushing with 30 ml saline. Time-of-flight MRA: TR = 25 ms, TE = 7 ms; FOV = 1.8 cm^2^; matrix size = 241 × 256; bandwidth = 100 Hz/PX; slice thickness =0.7 mm. Ischemic lesion was localized by taking clinical manifestations of patients with TIA into consideration.

Estimates of the volume of hypoperfusion on MRI perfusion scans are performed using the RAPID software, which is an automated image post-processing software (Rothwell et al., 2007; Wang et al., 2019a). Lesion volume of *T*_*max*_ ≥ 4 s ≥ 10 ml is used for determining perfusion deficits in patients with TIA (Liu et al., 2007; Najib et al., 2019). Two experienced radiologists independently evaluated the presence of acute ischemic lesions on DWI/PWI.

### Sample Size and Power Calculation

Two-sided chi-square test is performed at *P* = 0.05 (alpha) to compare the incidence of recurrent vascular events between patients with TIA with PWI-positive and PWI-negative findings. Previous studies have shown that 10% of patients with TIA will relapse; however, the pilot study showed that 34.8% of PWI-positive patients with TIA had recurrent TIA. With the testing power of 80%, the significance level of 0.05 (two-sided), and a 1:1 ratio, with a dropout rate of 5%, a total of 90 patients are needed to detect the difference in relative risks between patients with TIA with PWI negative and PWI positive findings.

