The morphological definition of TIA, that is, diffusion-weighted imaging (DWI)-negative TIA, did not clearly distinguish the tissue perfusion status of all patients with TIA. Low perfusion may be one of the mechanisms of TIA recurrence. Perfusion weighted imaging (PWI) is positive in 20–40% of patients with clinical TIA, while DWI is negative (Mlynash et al., 2009; Kleinman et al., 2012; Asdaghi et al., 2013; Grams et al., 2016; Lee et al., 2017). Previous studies have suggested that hypoperfusion might be associated with recurrent TIAs, stroke, and continued deterioration of neurological symptoms (Olivot et al., 2008; Asdaghi et al., 2011, 2013; Lee et al., 2017). The previous study conducted by the authors has assessed 66 patients with TIA with anterior circulation symptoms and found that hypoperfusion is present in 50% of the patients (33/66), with 31.8% (21/66) showing PWI-positive and DWI-negative findings (Wang et al., 2019b). In order to further explore whether the recurrence of TIA in patients with no lesions shown on DWI is related to hypoperfusion, 46 patients with normal DWI were followed up for 3 months in the study. The incidence of recurrent TIA was 41.2% (14/34) in the hypoperfusion group and 16.7% (2/12) in the normal perfusion group. There was a significant statistical difference between the two groups.

There are many modalities for assessing hypoperfusion. Although mean transit time (MTT) and time to peak (TTP) can be used to observe abnormal changes in perfusion in patients with TIA (Kleinman et al., 2012), time-to-maximum of residue function (*T*_*max*_) ≥ 4 s is currently the best one for evaluating perfusion abnormalities in the early stage (Olivot et al., 2009; Wang et al., 2019a,b). The previous results showed that the prevalence of *T*_*max*_ ≥ 4 s > 10 ml was 50% (33/66). Limb fatigue combined with *T*_*max*_ ≥ 4 s > 10 ml was an independent risk factor for recurrence (adjusted OR = 3.74, 95% CI = 1.02–13.64, *P* = 0.046). Therefore, it is feasible and clinically significant to use *T*_*max*_ ≥ 4 s to evaluate the perfusion status of patients with TIA.

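### The sample size pairs an all-TIA rate (10%) with the pilot's pooled rate (34.8%) as if they were PWI-negative and PWI-positive rates; the pilot's own group rates give about 71% power, not 80%

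*Protocol article*

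**What the plan says.** All references are to the protocol article.

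- **Sample Size and Power Calculation.** The planned test is a two-sided chi-square comparison of recurrence between PWI-positive and PWI-negative patients. Two rates are given. The first is general: "Previous studies have shown that 10% of patients with TIA will relapse". The second is presented as a subgroup rate: "the pilot study showed that 34.8% of PWI-positive patients with TIA had recurrent TIA". With 80% power and two-sided 0.05, the paragraph concludes that with "a 1:1 ratio, with a dropout rate of 5%, a total of 90 patients are needed". No rate is named as the PWI-negative rate.
- **Background.** The authors' earlier work followed 46 patients with normal DWI for 3 months. Recurrence was 41.2% (14/34) with hypoperfusion and "16.7% (2/12) in the normal perfusion group".
- **Abstract.** The primary outcome is recurrence of TIA within 7 days.

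**The concern.** A comparison of two groups needs a planning rate for each group. Here the comparator is a rate for TIA patients of any perfusion status, taken from previous studies, and the positive-group rate comes from the authors' pilot. The document contains only one recurrence rate for patients with normal perfusion, the pilot's 2/12, and the calculation does not use it. The figure that is taken from the pilot does not match the pilot's hypoperfusion rate either: 34.8% is what results when both perfusion groups are pooled.

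The stated 80% power therefore rests on a 24.8-point difference that no single source supports. If the study finds no difference, readers will weigh that result against a claimed 80% power which the document's own group data do not bear out.

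**Working it through.** **Inputs.** Two-sided alpha 0.05, 1:1 ratio, 5% dropout, N = 90, rates 10% and 34.8% (Sample Size and Power Calculation); pilot counts 14/34 and 2/12 (Background). Evaluable patients: 90 × 0.95 = 85.5, or 42.75 per group, taken as 43.

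**Formula** (pooled variance, no continuity correction). With p̄ = (p1 + p2)/2 and d = |p2 − p1|:

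z = [d√n − 1.96·√(2p̄(1 − p̄))] / √(p1(1 − p1) + p2(1 − p2)), and power = Φ(z).

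**Step 1: reproduce the plan.** p1 = 0.10, p2 = 0.348, n = 43:

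- p̄ = 0.224, d = 0.248, √(2p̄(1 − p̄)) = 0.5896, denominator 0.5629
- z = (0.248 × 6.557 − 1.96 × 0.5896)/0.5629 = 0.836, so power = 79.8%

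Solved for 80% power, n = 43.2 per group, 86.3 in total, and 86.3/0.95 = 90.9. The plan's 90 is recovered, which confirms that 10% was used as the PWI-negative rate.

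**Step 2: where 34.8% comes from.** (14 + 2)/(34 + 12) = 16/46 = 34.8%. The hypoperfusion group alone is 14/34 = 41.2%.

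**Step 3: can 10% be the rate of the whole cohort?** At 1:1 the positive half contributes 0.5 × 34.8% = 17.4 points. An overall 10% would need a PWI-negative rate of 2 × 10% − 34.8% = −14.8%, which is impossible. Under the plan's own pairing the overall rate is (10% + 34.8%)/2 = 22.4%. An overall 10% is compatible with 34.8% only if at most 10/34.8 = 28.7% of patients are PWI-positive, which is not 1:1.

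**Step 4: like-for-like pilot rates.** p1 = 0.167, p2 = 0.412, n = 43:

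- p̄ = 0.2895, d = 0.245, √(2p̄(1 − p̄)) = 0.6414, denominator 0.6175
- z = (0.245 × 6.557 − 1.96 × 0.6414)/0.6175 = 0.566, so power = 71.4% (exact power of the uncorrected chi-square test: 72.7%)

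For scale, 80% power at these rates needs 53 per group, 106 evaluable, and 106/0.95 = 111.6, or 112 patients.

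**Step 5: sensitivity to the PWI-negative rate**, with 41.2% in the positive group and 43 per group:

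| PWI-negative rate | Power |
|---|---|
| 10% | 93% |
| about 14.5% | 80% |
| 16.7% | 71% |

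**Step 6: precision of the pilot's PWI-negative rate.** The exact 95% interval for 2/12 is about 2% to 48%.

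**The case against.** The strongest defence is that N = 90 is arithmetically right for its inputs, and that the paragraph attributes the 10% to earlier studies without claiming it as the expected overall rate of this cohort. On that reading, Step 3 shows only that figures from different sources do not mix. This stands in part: the fault lies in the choice and labelling of the inputs, not in the calculation.

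A second defence is that 2/12 is too few patients to displace 10%, since its interval contains 10%. That also stands. The pilot does not refute 10%; it shows that a flat 80% is unsupported.

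A third is that the two input faults pull in opposite directions. Replacing 34.8% by 41.2% while keeping 10% raises power to 93%, so the all-patient origin of the 10% does not by itself prove optimism. This is correct, and it is why both inputs must be replaced together.

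A reader might draw three stronger conclusions that the document does not support:

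- *Power is only about 48%.* That figure comes from 34.8% against 16.7%. It sets a pooled rate against a subgroup rate, which is the same mismatch over again.
- *Power is 80% only if the PWI-negative rate is 10%.* This holds only with the mislabelled 34.8%. With 41.2% in the positive group, 80% is kept up to about 14.5%.
- *The 7-day primary comparison has 71% power.* The pilot rates are 3-month rates in DWI-normal patients. The document gives no 7-day rate by perfusion group, so power for that outcome cannot be computed from it.

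**Conclusion.** The concern holds as a fault in the planning inputs. The 10% is an all-TIA rate used as the PWI-negative rate, and the 34.8% is a pooled pilot rate labelled PWI-positive. With the pilot's own two group rates, N = 90 gives about 71% power, roughly 9 points below the stated 80%.

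This rests on 43 evaluable patients per group, an equal split and the uncorrected chi-square test. The split is an outcome of imaging and not under the investigators' control. The Discussion cites hypoperfusion shares of about 42% and 25%; with 86 evaluable patients these give about 71% and 64% at the pilot rates. The 71% is an illustration from small 3-month data, not a firm estimate, and it does not apply to the 7-day primary outcome.

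**What to change.** Keep N = 90 and rewrite the sample size paragraph:

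1. Replace both rates with a PWI-positive and a PWI-negative rate from one source. From the pilot these are 41.2% (14/34) and 16.7% (2/12). Drop the PWI-positive label from 34.8%, or identify that figure as the pooled rate.
2. Replace the flat 80% with about 71% at the pilot rates, and add the range with 41.2% in the positive group: about 93% at a PWI-negative rate of 10%, 80% at about 14.5%, and 71% at 16.7%.
3. State that these are 3-month rates in DWI-normal patients, that 2/12 has an exact 95% interval of about 2% to 48%, and that the power figure therefore describes the 3-month comparison and not the 7-day primary outcome.

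The 48% figure should not be printed in the protocol. The cost is one reworded paragraph and a less favourable stated power; no patients are added.

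### The 34.8% planned for PWI-positive patients contradicts the pilot's own 41.2% and equals its all-patient rate; with a comparator that is not PWI-negative either, the stated 80% power should become a justified range

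*Protocol article*

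**What the plan says.** All references are to the protocol article.

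- **Sample Size and Power Calculation, comparator.** The baseline rate is introduced with "Previous studies have shown that 10% of patients with TIA will relapse". It is not restricted to PWI-negative patients and carries no time horizon.
- **Sample Size and Power Calculation, exposed group.** Here "the pilot study showed that 34.8% of PWI-positive patients with TIA had recurrent TIA".
- **Sample Size and Power Calculation, design.** The test is a two-sided chi-square of PWI-positive against PWI-negative patients, with 80% power, "the significance level of 0.05 (two-sided), and a 1:1 ratio, with a dropout rate of 5"%. The total is 90 patients.
- **Background, pilot result.** For 46 patients with normal DWI followed for 3 months: "The incidence of recurrent TIA was 41.2% (14/34) in the hypoperfusion group and 16.7% (2/12) in the normal perfusion group". The next sentence adds: "There was a significant statistical difference between the two groups".
- **Background, earlier cohort.** Of 66 patients, 33 had hypoperfusion, "with 31.8% (21/66) showing PWI-positive and DWI-negative findings".
- **Abstract.** The primary clinical outcome is recurrence within 7 days of onset.

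**The concern.** The power calculation needs one recurrence rate for PWI-positive patients and one for PWI-negative patients. The document's own pilot supplies both, and neither is used. The figure labelled PWI-positive disagrees with the pilot's hypoperfusion rate and coincides with the rate over both groups together. The comparator describes TIA patients as a whole. As it stands, the calculation appears to set one all-patient rate against another from a different source.

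This matters because the calculation is the only support given for 90 patients. If the study finds no difference, readers will weigh that result against a claimed 80% power. The Background adds to the problem by presenting the pilot difference as statistically established. It also leaves unclear which patients the pilot counts came from.

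**Working it through.** **Inputs.** Two-sided alpha 0.05 (z = 1.960), power 80% (z = 0.842), 1:1 split and 5% dropout are from the sample size section. The planning rates of 34.8% and 10% are from the same section. The pilot counts 14/34 and 2/12 are from the Background. Evaluable patients: 90 × 0.95 = 85.5, or 42.75 per group (43 when rounded).

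**Formula.** Chi-square comparison with pooled variance and no continuity correction. With m patients per group and p̄ = (p1 + p2)/2:

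z_power = [√m·|p1 − p2| − 1.960·√(2p̄(1 − p̄))] / √(p1(1 − p1) + p2(1 − p2))

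**Step 1: the plan's own figure.** For 34.8% v 10%, p̄ = 0.224 and the two square-root terms are 0.5896 and 0.5629.

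- At m = 42.75: (6.538 × 0.248 − 1.960 × 0.5896)/0.5629 = 0.828, so power is 79.6%.
- Solving for 80% gives 43.2 per group, 86.3 in total, and 86.3/0.95 = 90.9 after dropout. Rounding up at each step gives 44 per group and 93 in total.

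The stated 90 patients and 80% power therefore follow, within rounding, from 34.8% v 10%.

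**Step 2: where 34.8% could come from.** (14 + 2)/(34 + 12) = 16/46 = 0.3478. The nearest fractions over the PWI-positive denominators in the Background do not give it: 12/34 = 35.3%, 11/33 = 33.3%, 7/21 = 33.3%.

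**Step 3: power with a PWI-positive rate of 41.2%.**

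| Rates (positive v negative) | Power at 42.75 per group | Power at 43 per group |
|---|---|---|
| 34.8% v 10% (plan) | 79.6% | 79.8% |
| 41.2% v 16.7% (both pilot rates) | 71.2% | 71.5% |
| 41.2% v 10% (all-TIA comparator kept) | 92.5% | 92.6% |

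For the pilot pair, p̄ = 0.2892 and the square-root terms are 0.6412 and 0.6173. At m = 42.75, (6.538 × 0.2451 − 1.960 × 0.6412)/0.6173 = 0.560, which is 71.2%. With all 90 evaluable it is 73.5%. Reaching 80% would take 53 per group, or 106/0.95 ≈ 112 in total.

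The absolute difference hardly moves (24.8 points planned, 24.5 in the pilot). Power falls in the second row because both rates are higher and the variance is larger.

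**Step 4: sensitivity to the comparator.** With 41.2% in PWI-positive patients and 43 per group, power is about 82% for a PWI-negative rate of 14%, 78% for 15%, 71% for 16.7% and 57% for 20%. The exact 95% interval for 2/12 is about 2% to 48%.

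**Step 5: the significance claim.** For 14/34 v 2/12, chi-square = 46 × (14 × 10 − 20 × 2)² / (34 × 12 × 16 × 30) = 2.35, P = 0.125. The continuity-corrected P is 0.24 and the Fisher P is 0.17. The Newcombe 95% interval for the difference runs from about −7 to +45 percentage points.

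**Step 6: the counts.** The 66-patient cohort has 33 patients with hypoperfusion, 21 of them DWI-negative. The follow-up has 34 DWI-normal patients with hypoperfusion. If the follow-up is a subset of that cohort under the same definition, 34 is impossible, since it exceeds both 21 and 33.

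**The case against.** The strongest reply has four parts.

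1. **The origin of 34.8% is not stated.** The sample size section says only that it comes from the pilot study and gives no denominator. Other fractions also round to 34.8%, such as 23/66 and 8/23, and the second could be a genuine PWI-positive subgroup. This stands: the link to 16/46 is an inference, although the most plausible one. The conflict between 34.8% and 41.2% does not depend on it if both sections describe the same pilot, and if they do not, the article needs to say so.
2. **A reader might infer that the study is underpowered, at 71%.** The document does not show that. Correcting only the PWI-positive rate raises power to about 93%. The whole of the fall comes from also replacing 10% by 2/12, which is very imprecise.
3. **A reader might infer that 41.2% and 16.7% are the right planning rates.** They are like for like only within the pilot. They are 3-month rates in patients with normal DWI, whereas the primary outcome is at 7 days and the inclusion criteria do not require a normal DWI.
4. **The pilot counts may come from a different cohort or definition, and the test behind the significance claim is not named.** Both are possible. The first calls for reconciliation, not a finding of error. On the second, none of the usual crude tests on the printed counts comes near 0.05, so the sentence needs either its test or a correction.

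The calculation itself contains no slip; the fault lies in its inputs. The Discussion's admission that the sample is relatively small does not repair them.

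**Conclusion.** The concern holds, with limits. The two sections give incompatible PWI-positive pilot rates, and 34.8% appears to be the pooled pilot rate mislabelled. The 10% is not a PWI-negative rate. The stated 80% power at 90 patients is what this mismatched pair yields, so it is not supported as power for the comparison the study will make.

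Taking 41.2% for PWI-positive patients, the document's figures support a range of about 71% (against 16.7%) to about 93% (against 10%) at roughly 86 evaluable patients. This assumes a 1:1 split, 5% dropout, an uncorrected chi-square test, and that the pilot study in the sample size section is the follow-up in the Background. Neither end is established for a 7-day outcome. The description of the pilot difference as significant is not supported by its printed counts (P = 0.125 to 0.24).

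**What to change.** - In the sample size section, relabel 34.8% as the all-patient pilot rate (16/46) if that is its source. Otherwise, give its numerator, denominator and origin.
- Reconcile that section with the Background, including the 34 hypoperfused patients among 46 against the 21 among 66. State whether the two sets of counts share a cohort and a definition of hypoperfusion.
- Replace the single 80% with power at about 86 evaluable patients for stated group-specific rates: about 71% for 41.2% v 16.7% and about 93% for 41.2% v 10%. Present these as a range, and say that 16.7% rests on 2/12 and that 10% is a general TIA rate.
- Justify the assumed rates for recurrence at 7 days, or declare the calculation to be one for 3-month recurrence.
- In the Background, delete the claim of a significant difference or correct it with the test used, P of 0.125 (chi-square) or 0.17 (Fisher), and the interval of about −7 to +45 points.

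The cost is a reworded paragraph, one corrected sentence, and a stated power that is less favourable or less certain. No additional patients, visits or data are needed.

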## Abstract

**Background:** Transient ischemic attack (TIA) has a high incidence of recurrent vascular events. Hypoperfusion is one of the factors that are closely correlated with 7-day recurrence of TIA. This study aimed to evaluate the power of hypoperfusion shown on magnetic resonance (MR) perfusion imaging in predicting the incidence of 7-day recurrence of ischemic events after TIA.

**Methods/Design:** REATTACK is a prospective multi-centered cohort study on the correlation between MR perfusion and TIA recurrence. Ninety patients aged ≥18 years with recent (<7 days after onset) clinical TIA will be continuously included. All the patients will undergo diffusion-weighted imaging (DWI) and perfusion-weighted imaging (PWI) assessments within 24 h after the onset of TIA. The subjects will then be divided into a PWI positive group and a PWI negative group according to the time-to-maximum of the residue function (*T*_*max*_). PWI will be repeated after 7 days and in 3 months. The primary clinical outcome will be the recurrence of TIA within 7 days after the onset of TIA. Secondary outcomes will be the recurrence of TIA in 3 months and modified Rankin scale (mRS) score. A chi-square test will be performed to compare the difference in the incidence of recurrent TIA between the two groups, and rank sum test in the mRS score. Multivariate logistic regression will be simultaneously performed to analyze the risk factors for the recurrence of TIA.

**Discussion:** The results of this study will confirm whether abnormal *T*_*max*_ helps to identify the patients with TIA who have high risks of recurrent ischemic events. This would largely improve the prognosis of patients with TIA.

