## Background

Transient ischemic attack (TIA) has been defined as a short-lasting episode of neurological dysfunction without evidence of acute infarction (Easton et al., 2009). Approximately 24 million people experience TIA every year in China (Wang et al., 2015). Patients with recent TIAs are at a high risk for recurrent strokes or other vascular events (Lavallee et al., 2007; Amarenco et al., 2016). For example, patients with TIA have a 4–10% possibility of developing a stroke within 7 days and a 10–20% (average 11%) possibility within 90 days, much higher than the risk of developing recurrent strokes (2–7%, average 4%) within 90 days after an acute ischemic stroke (Kelly et al., 2016). Urgent diagnosis and treatment can significantly reduce the risk of recurrent ischemic events after TIA (Amarenco et al., 2016; Kim et al., 2016). A cohort study in the UK showed that optimal secondary prevention decreased the incidence of recurrent ischemic events after TIA from 10.3 to 2.1% (Rothwell et al., 2007).

A recent study raised the hypothesis that patients with TIA have different degrees of recurrence, depending on clinical symptoms, pathological mechanisms, and treatments (Kelly et al., 2016). How to identify TIA patients at high risk of recurrence and provide timely treatment is a problem that needs to be solved urgently in the clinic. The age, blood pressure, clinical symptoms, duration, and diabetes score (ABCD2, 0–7 points) is a stratified approach based on clinical manifestations. It aims to facilitate the evaluation of patients with stroke/TIA by non-neurology medical staff in the emergency room. For neurology professionals, its specificity is low (Amarenco et al., 2009; Giles and Rothwell, 2010; Wardlaw et al., 2015).

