### Objectives

#### Primary Objective

▪   To assess the added diagnostic value of hypoperfusion demonstrated on PWI in predicting recurrent vascular events of patients with TIA within 7 days.

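### The 80% power claimed for 90 patients is not supported for the 7-day primary comparison: the 34.8% behind it matches a 3-month pilot rate pooled over both perfusion groups

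*Protocol article*

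**What the plan says.** The Abstract fixes the horizon of the primary outcome: "The primary clinical outcome will be the recurrence of TIA within 7 days after the onset of TIA". The Primary Objective uses the same window: "in predicting recurrent vascular events of patients with TIA within 7 days". Three-month recurrence is secondary in the Abstract ("Secondary outcomes will be the recurrence of TIA in 3 months and modified Rankin scale (mRS) score"), although Study Design lists both horizons together as main outcomes.

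The Sample Size and Power Calculation section plans a two-sided chi-square test at 0.05. Its two rates are 10%, attributed to earlier studies of TIA patients, and a pilot figure: "the pilot study showed that 34.8% of PWI-positive patients with TIA had recurrent TIA". Neither carries a time window. With 80% power, a 1:1 ratio and 5% dropout, the section concludes that "a total of 90 patients are needed to detect the difference in relative risks" between the two PWI groups.

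The only pilot recurrence data described are in the Background: "46 patients with normal DWI were followed up for 3 months in the study", with recurrence in 14/34 (41.2%) of the hypoperfusion group and 2/12 (16.7%) of the normal-perfusion group.

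**The concern.** A power statement belongs to an outcome and its window. The primary comparison is at 7 days, but the pilot rate that drives the calculation appears to have accrued over 3 months. Cumulative recurrence at day 7 cannot exceed recurrence at 3 months, and the calculation has no slack: any PWI-positive rate materially below 34.8% against 10% takes power under 80%.

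The rate also appears to be misdescribed. It matches the pooled pilot rate, not the PWI-positive one, so the contrast is not the one seen in the pilot at either horizon.

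What is at stake is how a null 7-day result is read. Under a claimed 80% power it would look like evidence that hypoperfusion does not predict early recurrence, when the study may have had little chance of showing a difference.

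**Working it through.** **Inputs.** 34.8%, 10%, two-sided alpha 0.05, 80% power, 1:1 and 5% dropout come from the sample-size section. 14/34 and 2/12 over 3 months come from the Background. Analysable patients: 90 × 0.95 = 85.5, about 43 per group.

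**1. Reproduce the 90.** Arcsine formula: h = 2·arcsin√0.348 − 2·arcsin√0.10 = 1.2619 − 0.6435 = 0.6184. Then n = 2 × [(1.960 + 0.842)/0.6184]² = 41.05, so 42 per group; 42/0.95 = 44.2, so 45 per group and 90 in total. The pooled-variance formula gives 44 per group, or 93 after dropout. The stated total follows from the stated inputs.

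**2. Power at 43 per group.** The formula, with p̄ the mean of the two rates, is

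power = Φ{[|p1 − p0|·√n − 1.96·√(2p̄(1 − p̄))] / √(p1(1 − p1) + p0(1 − p0))}.

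For 34.8% v 10%: p̄ = 0.224 and (1.6262 − 1.96 × 0.5896)/0.5629 = 0.836, so power is 79.8%.

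**3. Trace the 34.8%.** (14 + 2)/(34 + 12) = 16/46 = 34.8%. The PWI-positive rate alone is 14/34 = 41.2%. The match is with the pooled 3-month rate.

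**4. Power at 3 months on the pilot's own group rates.** For 41.2% v 16.7%: p̄ = 0.2895 and (1.6066 − 1.96 × 0.6414)/0.6175 = 0.566, so power is about 71%. Reaching 80% would take 53 per group, or 112 in total after dropout.

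**5. Power at 7 days (assumptions only).** No 7-day TIA recurrence rate by PWI group is given. Suppose a fraction f of both assumed rates applies at day 7, which keeps the relative risk at 3.48. Expected events are 43 × (p1 + p0).

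| f | PWI+ v PWI− | Power at 43 per group | Expected events |
|---|---|---|---|
| 0.25 | 8.7% v 2.5% | 24% | 4.8 |
| 0.40 | 13.9% v 4.0% | 36% | 7.7 |
| 0.50 | 17.4% v 5.0% | 44% | 9.6 |
| 0.75 | 26.1% v 7.5% | 64% | 14.4 |
| 0.91 | 31.7% v 9.1% | 75% | 17.5 |

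The total needed for 80% power, with dropout, runs from 453 (f = 0.25) to 133 (f = 0.75). The 0.91 is 10/11, the most favourable ratio obtainable from the Background's stroke figures (step 6).

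If instead 10% is already a 7-day comparator and only the PWI-positive rate is lower, 25% v 10% gives about 45% and 20% v 10% about 25%.

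**6. Can f be fixed from the documents?** The Background says that "patients with TIA have a 4–10% possibility of developing a stroke within 7 days and a 10–20% (average 11%) possibility within 90 days". These are stroke risks in all TIA patients. Pairing low with low and high with high gives 4/10 to 10/20, or 0.40 to 0.50. Dividing by the 90-day average gives 4/11 to 10/11, or 0.36 to 0.91. The answer depends on the pairing, and neither version concerns TIA recurrence by perfusion group.

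**The case against.** The strongest points on the other side are these.

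- **The window of the 34.8% is not stated.** Its 3-month origin is an inference. That stands as a caveat. But the match to 16/46 is exact, and no other pilot recurrence data are described.
- **The 10% may already be a 7-day figure.** This also stands: 10% is the top of the Background's 7-day stroke range and the bottom of its 90-day range. It does not rescue the claim, because 80% against 10% still needs essentially the whole 34.8% to occur in week one.
- **Correcting only the label would raise power.** 41.2% v 10% gives more than 90%. But that sets a 3-month rate in PWI-positive patients against an undated figure for TIA patients in general, when the pilot's own normal-perfusion rate was 16.7%. That rate rests on 2/12, so the 71% is itself imprecise.
- **The arithmetic is right.** It is. The fault is a mismatch between input and outcome, not a miscalculation.

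A reader might also draw two stronger conclusions that the documents do not support. One is that 7-day power is 30–45% on the protocol's own ratio; the protocol gives no such ratio, and that range comes from one pairing of stroke-risk limits and from treating the undated 10% as a 3-month rate. The other is that the 80% is valid for the 3-month outcome, so that relabelling it or exchanging the outcomes would settle the matter. On the pilot's group rates 3-month power is about 71%, and an exchange would also replace the study's stated 7-day question.

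**Conclusion.** The point holds as an unsupported power claim. The 90 follows from its inputs, but those inputs are not shown to describe the 7-day primary comparison, and the PWI-positive label does not fit the pilot data. The mismatch can be stated with confidence; the size of the loss cannot. Under the labelled assumptions, 7-day power lies between about 24% and 75%, and it reaches 80% only if essentially all of the assumed recurrence falls in the first week. At 3 months it is about 71% on the pilot's group rates. All figures assume 43 analysable patients per group, the planned 1:1 split and an uncorrected two-sided test at 0.05.

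**What to change.** In the Sample Size and Power Calculation section:

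1. State the source, denominator and time window of both the 34.8% and the 10%.
2. Correct the PWI-positive label if 34.8% is the pooled 16/46.
3. Withdraw the 80% claim for the 7-day primary outcome.
4. Restate power at 90 patients separately for each horizon: for 7 days, a range under labelled assumptions such as the table above; for 3 months, about 71% on the pilot group rates.
5. Say that the 7-day result will be reported as an estimate with a confidence interval, and that a null result will not be read as evidence of no association.

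The cost is a reworded paragraph and a less favourable stated power. No new patients or visits are needed.
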